### Work package I: claims data of persons with and without mental illnesses

The insured persons’ data are anonymized by TK-NRW and are made available to the LVR-IVF for the analyses.

Claims data of persons with at least one of the following common somatic diagnoses (only confirmed diagnoses, ICD-10 code (German Modification)): thyroid disease (E01–E07), obesity (E66), chronic ischaemic heart disease (I25), arterial hypertension (I10–I15), type 2 diabetes mellitus (E11), stroke (I60–I64), or breast cancer (C50) *and no diagnosis of a mental disorder* (F00–F99)).Billing data of patients with at least one of the aforementioned common somatic diagnoses *and* concurrent healthcare service use (documented in the same billing quarter) due to a *confirmed diagnosis of a mental disorder* (F00–F99).

The number of persons insured with TK-NRW amounts to 2.6 million. According to the Robert Koch-Institute (2017), the prevalence of hypertension in Germany is 30.9% in women and 32.8% in men [22]. According to the Association of Statutory Health Insurance Physicians in the Federal Republic of Germany, insured persons with arterial hypertension according to ICD-10 were the most frequent cases of treatment in medical practices in the North Rhine region in 2021, at 34.1% [23]. We therefore also assume that arterial hypertension is the most common somatic disease among persons insured with TK-NRW, according to the somatic inclusion criteria mentioned above. Based on data for 2015, we estimated in the project proposal that approximately (approx.) at least 40% (n = 1,040,000) of persons insured with TK-NRW have a somatic disease according to the abovementioned inclusion criteria. TK-NRW estimates that 12–15% of the persons insured with TK have a psychiatric diagnosis that requires inpatient or outpatient treatment. Consequently, we estimate that at least 10% of patients who meet the inclusion criteria of the abovementioned somatic diagnosis groups also have a mental disorder (n = 104,000).

The power calculations show that with group sizes of n_1_ = 936,000 (secondary data of persons insured by TK-NRW with somatic diseases according to the inclusion criteria described above and without comorbidity of a mental disorder) and n_2_ = 104,000 (secondary data of persons insured by TK with somatic diseases according to the inclusion criteria described above and with comorbidity of a mental disorder), a power of 90%, an alpha of 0.05, and a sensitivity of |d| = 0.01 (Cohen’s d = 0.01) can be achieved.

Inferential statistical procedures such as T-tests, chi-square tests, and further statistical procedures will be used to compare the groups. In particular, differences between the groups of insured persons with somatic and mental illnesses compared to the group of persons with somatic illnesses only, as well as differences between the subgroups of insured persons with different mental illnesses, will be examined. Regression analyses with clinical and socio-demographic co-factors are planned in order to examine outcomes such as cumulative length of stay in inpatient psychiatric treatment, cross-disciplinary care, diagnostic/therapeutic services, therapy density, and mortality. Based on these analyses, associations between healthcare utilization (e.g. utilization rates of psychiatric-psychotherapeutic and somatic care specialists) and outcomes (e.g. Frequency of disability, rates of retirement due to reduced earning capacity, mortality rates) will be analysed. Statistical tests are performed using the Statistical Package for the Social Sciences (SPSS).

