**Methods:**

The study is conducted as a mixed-methods approach and will include (a) descriptive and inferential analysis of secondary claims data of persons insured by a German statutory health insurance company in North Rhine-Westphalia (Techniker Krankenkasse, TK-NRW), (b) qualitative individual interviews and group discussions, and (c) based on (a) and (b), quantitative surveys of both patients and physicians. We intend to analyse a sample of claims data of about 2.6 million persons insured by TK-NRW (group comparisons between TK-NRW insured persons with a diagnosis of a prevalent somatic disease [ICD-10-GM E01–E07, E11, E66, I10–I15, I20–I25, I60–I64] with and without comorbidity of a mental disorder [F00–F99]), in order to assess the uptake of somatic care by people with mental and somatic comorbidity. In addition, primary data from patients with the aforementioned somatic illnesses and a mental comorbidity as well as primary data from physicians (general practitioners and medical specialists) will be collected. The focus here will be on support factors and barriers in the somatic care of people with mental comorbidity.

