The somatic care of patients with mental comorbidity is quantitatively and qualitatively different to the somatic care of patients without mental comorbidity.

Secondary hypotheses.

2.Mental and somatic multimorbidity is a barrier to the somatic care of people with mental illnesses.3.Certain SMIs, such as schizophrenia, are more often a barrier to somatic care than other mental illnesses.4.Transitional barriers at the interfaces between in Germany traditionally segregated inpatient and outpatient care sectors represent a barrier to the provision of care.5.Good health literacy is beneficial for the somatic care of patients with mental comorbidity.6.Good social integration has a positive correlation with somatic care of patients with mental comorbidity.7.Characteristics of the treating physicians (professional experience, prejudices) can be associated with the somatic care of patients with mental comorbidity.

The primary hypothesis as well as the secondary hypotheses 2–4 will be investigated by analysing the claims data of persons insured with the TK-NRW (WP I). The primary data from interviews and questionnaires is expected to provide relevant content and constructs for the secondary hypotheses 4–7 (WP II – V).

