## Methods/design

This study is performed by the LVR-Institute of Healthcare Research (LVR-IVF) in cooperation with the LVR-Clinic Düsseldorf and the Techniker Krankenkasse North Rhine-Westphalia, division of a German Statutory Health Insurance Company (TK-NRW).

The SoKo study includes persons who have already made use of the healthcare system due to common somatic diseases (thyroid gland, arterial hypertension, type 2 diabetes mellitus, obesity, coronary heart disease, stroke, and breast cancer (ICD-10-GM E01–E07, E11, E66, I10–I15, I20–I25, I60–I64, C50)). These somatic diseases include both acute and chronic conditions, which require different types of outpatient, inpatient and rehabilitative care. We will study the somatic care of persons who suffer from at least one of these somatic diseases and compare it to the care of persons who suffer from at least one of these somatic diseases and are also diagnosed with a mental disorder (ICD-10-GM F00–F99). All participants are insured with TK-NRW. TK-NRW will provide anonymised claims data of all members who are diagnosed with at least one of the aforementioned somatic disorders. We will compare the data of persons without a mental disorder and persons who are diagnosed with at least one of the aforementioned somatic disorders and a mental disorder (WP I). In addition, TK-NRW will invite a number of members who are diagnosed with at least one of the aforementionfed somatic illnesses and a mental disorder to participate in the guideline-based interviews and the survey study (WP II and IV). Moreover, we will conduct guideline-based interviews, focus groups, and a survey among general practitioners (GPs) and medical specialists in internal medicine, psychiatry, psychotherapy, and psychosomatics (WP III and V).

The following inclusion criteria will be applied:

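### Only the comorbid group must meet a same-quarter condition, which tends to select frequent users and can bias contact-based comparisons in WP I; the size cannot be derived from the article.

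*Protocol article*

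**What the plan says.** The article describes the WP I groups in three places, and they do not agree.

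- **Work package I, inclusion criteria.** The comparison group has at least one confirmed listed somatic diagnosis "and no diagnosis of a mental disorder". The comorbid group (called Ib later in the article) has a listed somatic diagnosis and "concurrent healthcare service use (documented in the same billing quarter") because of a confirmed F00–F99 diagnosis.
- **Methods/design.** The comorbid group is given as "persons who are diagnosed with at least one of the aforementioned somatic disorders and a mental disorder (WP I"), with no same-quarter condition. The entry condition common to both groups is prior care: "The SoKo study includes persons who have already made use of the healthcare system due to common somatic diseases".
- **Work package I, group sizes.** The base is "at least 40% (n = 1,040,000) of persons insured with TK-NRW have a somatic disease". At least 10% of these, 104,000, are expected to have a mental disorder as well. The power statement sets 936,000 without against 104,000 with mental comorbidity.

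Use of care is central to the comparison. The Abstract gives the purpose of the group comparison as "in order to assess the uptake of somatic care by people with mental and somatic comorbidity". The primary hypothesis in Background reads "The somatic care of patients with mental comorbidity is quantitatively and qualitatively different to the somatic care of patients without mental comorbidity". The WP I outcomes include "cross-disciplinary care, diagnostic/therapeutic services, therapy density, and mortality".

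**The concern.** Both groups need at least one somatic contact. The comorbid group alone must also show a coincidence in time. The chance that a somatic code and an F code share a quarter rises with the number of contacts, so somatic contact frequency helps to decide who enters that group and is also part of what is compared. Persons with few contacts are the most likely to fail the condition, and the comorbid group would then appear to use more somatic care than it does.

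The Background section cites reduced use of somatic services among people with severe mental illness. A selection effect towards higher use would work against seeing such a pattern. Ib is also the sampling frame for the patient interviews (WP II) and the patient survey (WP IV), so the definition reaches beyond the claims analysis.

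**Working it through.** **1. The plan's own figures.**

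Sizes: 0.40 × 2,600,000 = 1,040,000; 0.10 × 1,040,000 = 104,000; 1,040,000 − 104,000 = 936,000. The two groups use up the whole somatic population. The 104,000 is derived from having a mental disorder, not from same-quarter use.

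Detectable difference at 90% power and alpha 0.05, two-sided (the article does not state the sidedness):

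d = (1.960 + 1.282) × √(1/936,000 + 1/104,000) = 3.2415 × 0.0032686 = 0.0106.

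One-sided: 2.9264 × 0.0032686 = 0.0096. Both round to the stated 0.01.

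**2. Who falls where under the literal criteria.**

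| Somatic code | F code | Comparison group | Ib |
|---|---|---|---|
| any quarter | none | yes | no |
| Q1 | Q1 | no | yes |
| Q3 | Q1 only | no | no |

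The third row has no place in a split that sums to 1,040,000. If the absence of an F diagnosis were judged quarter by quarter, these persons would enter the comparison group instead, which is misclassification rather than loss.

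**3. Size of the selection effect under a true null.**

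The article gives no contact or coding rates, so every input here is an assumption: 4 quarters; gamma-Poisson contacts with frailty variance 0.5; somatic and mental contacts independent; true somatic use identical in both groups; exposure and outcome counted in the same window. Comparison group: at least one somatic contact. Ib: at least one quarter with both codes. The spurious d is (mean in Ib − mean in comparison group) / √(average of the two variances). Shared coding is the share of somatic contacts that also carry the F code.

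| Somatic / mental contacts per year | Shared coding | Mean, comparison | Mean, Ib | Mean, neither group | Comorbid persons lost | d, same quarter | d, any F code in window |
|---|---|---|---|---|---|---|---|
| 2 / 1 | 0% | 2.66 | 3.19 | 1.87 | 39.9% | 0.27 | 0.00 |
| 4 / 2 | 0% | 4.50 | 5.08 | 2.38 | 21.5% | 0.17 | 0.00 |
| 4 / 2 | 20% | 4.50 | 5.06 | 1.89 | 11.4% | 0.17 | 0.06 |
| 8 / 4 | 0% | 8.35 | 8.76 | 2.96 | 7.5% | 0.07 | 0.00 |
| 8 / 4 | 20% | 8.33 | 8.73 | 2.14 | 3.9% | 0.06 | 0.02 |

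With windows of 4 or 8 quarters and frailty variance 0.5 or 1, separate coding gives d of about 0.04 to 0.3. If 50% of somatic contacts carry the F code, the lower end falls below 0.01.

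**4. Carried-forward somatic diagnoses.**

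Example: 1 somatic and 0.5 mental contacts per quarter, 4 quarters, frailty variance 1, at least one somatic contact required. The somatic diagnosis is now also recorded in a stated share of the quarters with a mental contact.

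| Share | Ratio of means | d | Lost |
|---|---|---|---|
| 0% | 1.15 (5.74 / 5.00) | 0.16 | 21% |
| 50% | 1.05 | 0.06 | 9% |
| 90% | 1.00 | 0.00 | 1.5% |

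Under some carry-forward assumptions the excess reverses. With no carry-forward, keeping the same-quarter rule but counting outcomes in a later period lowers d from 0.16 to 0.12.

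**5. Power.**

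If 10%, 20% or 40% of the 104,000 were lost, the two-sided detectable d would be 0.0111, 0.0117 or 0.0134. The issue is bias, not precision.

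**The case against.** The case on the other side is substantial.

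- **The rule is easier to meet than it first looks.** It asks for a somatic diagnosis plus service use for an F diagnosis, not for two separate visits. One contact coding both is enough, and so is a long-term somatic diagnosis recorded again at a mental-health contact. Most of the listed diseases are long-term. This stands, and step 4 shows that it can remove the effect.
- **Methods/design and the exhaustive split suggest a two-way classification.** Methods/design also says that the insurer delivers data on all members with a listed somatic diagnosis, so persons with off-quarter codes may be in the file. This stands too. It makes the texts inconsistent and does not settle which definition applies.
- **Requiring concurrent treatment is a defensible definition of comorbidity.** It is, but here it is applied to one group only.
- **Observation and outcome windows may be set in a fuller document.** Their absence from the article is no finding. A later outcome window shrinks the bias without removing it in the example above.
- **Regression with co-factors is planned.** Clinical and socio-demographic covariates do not in general undo selection on contact frequency.

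A reader might infer that the rule will hide or reverse under-use that the study is meant to detect. The documents do not support that. The primary hypothesis is non-directional, the size and even the sign depend on coding practice that the article does not report, and part of the bias can remain under an any-F rule (d of 0.02 to 0.11 with 20% shared coding). Nor should d = 0.01 be read as a threshold of relevance. It follows from the sample size.

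**Conclusion.** The point holds as a fault in a stated rule. Entry to the comorbid group depends on a coincidence that grows more likely with contact frequency, and the comparison group has no matching condition. Contact-based outcomes are exposed to this; mortality is affected less directly. That some persons belong to neither group follows from the literal inclusion criteria only, and it conflicts with Methods/design and with the 936,000 + 104,000 split.

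The likely direction is an overstatement of somatic use in the comorbid group. Under a true null, d is about 0.04 to 0.3 if somatic and mental contacts are coded separately, and it can be near nil where diagnoses are routinely coded together or carried forward. These are illustrations on assumed contact rates, not estimates for this insurer. With a comparison able to detect d of about 0.01, even a small residual bias would probably reach statistical significance.

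**What to change.** 1. Reconcile Methods/design, the WP I inclusion criteria and the WP I group sizes, so that one definition of mental comorbidity applies throughout.
2. Define mental comorbidity as a confirmed F diagnosis in any quarter of a fixed baseline period, whatever the quarter of the somatic diagnosis. Define the comparison group as no F diagnosis in that same period.
3. Count utilisation in the period that follows. This reduces the bias but may not fully remove it if diagnoses are coded at shared contacts, and the report should say so.
4. Report how many persons have both diagnoses only in different quarters, with their somatic contact counts.
5. Keep the same-quarter definition as a sensitivity analysis.

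Cost: a change of definition at extraction or analysis, on claims that already carry the billing quarter. Some follow-up time is given up to the baseline period, and the 104,000 may change slightly. No new participants are needed.

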### Work package II: qualitative data of persons with mental illnesses

Access to insured persons who meet the inclusion criteria mentioned under Ib) will be provided by the statutory health insurance company TK-NRW. The mailing addresses are determined of TK-NRW on a key date in the survey period. The selection and postal dispatch is carried out by TK-NRW. We expected to find 104,000 persons who meet the inclusion criteria. Based on the experience of the TK headquarters in previous health services research projects, a response rate of approx. 15% is expected. We estimate that a sample of 500 insured persons will be sufficient to achieve a sample size of about 50 (10%) for individual interviews (telephone and video based).

The insured persons are contacted via TK-NRW in order to increase the willingness to participate. A financial incentive is offered and the relevance of the topic is emphasized in the invitation letter to appeal to the intrinsic motivation of the respondents.

### Work package III: qualitative data of outpatient physicians

To identify factors associated with the somatic care of people with comorbid mental illnesses, focus groups will be conducted with i) medical specialists of psychiatry and psychotherapy, neurology, psychosomatic medicine and psychotherapy, and psychotherapists and ii) and General practitioners (internists and General practitioners) from NRW. According to information from the North Rhine Medical Association (Ärztekammer Nordrhein – ÄKNO) and the Westphalia-Lippe Medical Association (Ärztekammer Westfalen-Lippe – ÄKWL), there are 12,957 general practitioners and specialists with the abovementioned groups in NRW (date of data query at the ÄKWL: 12 November 2019; at the ÄKNO: 19 November 2019). A representative sample of 500 specialists representing approx. 4% of all specialists in NRW will be contacted by post and will be invited to participate in a focus group. A response rate of 10% is expected (approx. 50 participants). The mail addresses will be obtained via internet searches. Factors such as practice location, gender, and specialist discipline will be taken into account when setting up the focus groups (purposeful sampling).

In order to increase the willingness to participate, additional recruitment methods will be used (advertisement at scientific and medical specialist congresses, newsletters of professional associations, personal contacts) and financial incentives will be offered. The relevance of the topic is emphasized in the invitation to participate in order to appeal to the intrinsic motivation of the respondents. In order to ensure transparency for providers a project homepage will be set up.

All individual interviews and focus groups in the work packages II and III are digitally recorded with the consent of the participants, professionally transcribed, pseudonymised, and analysed according to Kuckartz [24]. The aim of the qualitative analyses according to Kuckartz [24] is to develop both inductive and deductive categories that map the data material. In the first step, the category system is formed on the basis of the interview guide and thus follows a deductive category formation. In a second step, new aspects expressed by the interview/focus group’s participants are used for inductive category formation. Since reflexivity of data interpretation and interpersonal consensus-building are central principles of qualitative procedures, several measures are taken for quality assurance: the analysis of the interview material is carried out independently by two researchers (psychologists). This will be followed by consensus-building of the research team (psychologists, social scientist and public health economist). The categories that have been worked out will be discussed in a joint discourse within the research group in order to arrive at an in-depth analysis. To implement the exploratory approach of the primary data collection and the mixed-methods approach, the possible factors modifying the utilization and quality of somatic care of the mentally ill persons identified in work packages II and III will underlie the subsequent development of the questionnaires for work packages IV and V.

### Work package IV: Quantitative data of persons with mental illnesses

Access to insured persons who meet the inclusion criteria mentioned under Ib) will be provided by the statutory health insurance company TK-NRW. The mailing addresses are determined of TK-NRW on a key date in the survey period. The selection and postal dispatch is carried out by TK-NRW. We expected to find 104,000 persons who meet the inclusion criteria. Based on the experience of the TK headquarters from previous health service research projects, a response rate of approx. 15% is expected. We estimate that a sample of 20,000 insured persons will be sufficient to achieve a sample size of about 3,000 (15%) for the anonymous online survey.

The following power calculation refers to independent t-tests. The power calculations show that with group sizes of n_1_ = 104,000 (claims data of TK patients with somatic diseases according to the inclusion criteria described under Ib) and n_2_ = 3,000 (planned number of cases with 15% response rate), a power of 90%, an alpha of 0.05, and a sensitivity of |d| = 0.06 (Cohen’s d = 0.06) can be achieved.

The questionnaire will be developed based on literature research, the results of the qualitative interviews with patients, and the results from the interviews/focus groups with specialists. The questionnaire will furthermore be based on both validated scales and the authors’ own developments based on the qualitative work packages. The barriers to somatic care (secondary hypotheses 2 and 3) can be determined, for example, by the number of outpatient appointments. Transitional barriers at the interfaces between inpatient and outpatient care sectors will be identified in more detail in addition to the secondary claims data and primary data from the providers and insured persons (secondary hypothesis 4). The health literacy of patients can be investigated, for example, by surveying the functional, communicative, and critical health literacy of patients secondary hypothesis 5) [25, 26]. The social inclusion of people with chronic mental illness will be related to healthcare service utilisation as measured by the number of outpatient appointments or medication compliance (secondary hypothesis 5). The questionnaires will be subjected to a pretest before being used with patients in order to gain insight into the processes that occur in the respondents when answering the questions [27].

Difficulties may arise regarding the willingness to participate in the survey. For this reason, the insured persons are contacted via TK-NRW. Furthermore, the number of insured persons contacted is set high enough that an insufficient number of respondents is unlikely. Should this nevertheless be the case, a further survey wave can be initiated. To ensure transparency for insured persons a project homepage will be set up.

